#### Primary Outcome Measures

The primary outcome of the study will be feasibility as assessed by the proportion of eligible patients with emergency presentations who have devices as well as recruitment and retention rates.

#### Secondary Outcome Measures

Secondary outcomes measures include measures of epidemiology and physiology:

We will report trends for heart rate and step count, specifically the difference between the heart rate at home 24 hours, 1 week, and 1 month before clinical assessment from the wearable device compared with the first vital signs measured on admission to acute care as both an absolute and a proportional change.

We will also describe the degree of association between changes to vital signs from the community to assessment in acute care services with admission to a general ward or admission to a critical care area or discharge home within 24 hours from the time of the first hospital assessment.

The population wearing or carrying devices will be described in terms of gender, age, ethnicity, level of education, and digital literacy and contrasted with data from national surveys.

### Administrative Aspects, Monitoring, and Publication

#### Handling and Storage of Data and Documents

Data will be anonymously recorded in a research database (ie, Castor Electronic Data Capture System) in line with local data protection regulations, including but not limited to European General Data Protection Regulations (GDPR).

The collected data will be subsequently stored on a digital research environment from the Erasmus MC, a secure server with 2-factor authentication. There are no patient identifiers within the data. Only selected investigators of this study will have access to the server with the data. Data will be stored for 15 years.

#### Amendments

Amendments are changes made to the research after a favorable opinion by the accredited MEC has been given. All amendments will be notified to the ethics committee that gives a favorable opinion.

#### Annual Progress Report

The sponsor or investigator will submit a summary of the progress of the trial to the accredited MEC (Medisch Ethische Toetsings Commissie, METC) once the study is completed or, at the latest, after 1 year. Information will be provided on the date of inclusion of the first participant, the numbers of participants included and the numbers of participants that have completed the trial, serious adverse events or serious adverse reactions, other problems, and amendments.

#### Temporary Halt and (Premature) End of Study Report

The investigator or sponsor will notify the accredited METC of the end of the study within a period of 8 weeks. The end of the study is defined as the last patient’s last visit.

The sponsor will notify the METC immediately of a temporary halt of the study, including the reason of such an action.

In case the study is ended prematurely, the sponsor will notify the accredited METC within 15 days, including the reasons for the premature termination.

Within 1 year after the end of the study, the investigator or sponsor will submit a final study report with the results of the study, including any publications or abstracts of the study, to the accredited METC.

#### Public Disclosure and Publication Policy

The results of this study will be published in one or more peer-reviewed articles. Publications will be coordinated by the investigators or sponsors. Authorship of publications will be determined in accordance with the requirements published by the International Committee of Medical Journal Editors and in accordance with the requirements of the respective medical journal.

#### Benefits and Risks Assessment and Group Relatedness

There are no benefits or risks for participants of this study. The burden of participation in this study is low.

### Ethical Considerations

#### Regulation Statement

The study will be conducted in compliance with the principles of the Declaration of Helsinki (version 10, October 19, 2013) and the principal of Good Clinical Practice. Participants are not subject to procedures or required to follow rules of behavior and, as no additional data are collected the Medical Research Involving Human Subjects Act (also known by its Dutch abbreviation WMO) is not applicable to this study. Each principal investigator is responsible for ensuring that the study is performed in accordance with the protocol and Good Clinical Practice.

The review board of the Erasmus University Medical Center, Erasmus MC in Rotterdam, the Netherlands, has reviewed the research proposal. It confirmed that the rules laid down in the WMO, do not apply to this research proposal Medical Ethics Committee (MEC-2022-0795). The protocol (V1.2 17 February 2025) passed the required approvals in the United Kingdom Integrated Research Application System (IRAS 321129).

#### Recruitment and Consent

Patients eligible for inclusion are asked if they use a smartwatch or other wearables that measure heart rate by a collaborator of the study. If they do they fulfill the inclusion criteria, and they will then be informed about the study procedures and asked to participate after they have read the patient information form. After receiving this form patients will be asked if they will agree to sign written informed consent.

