**Inclusion criteria**
Participants in this study must be able to give informed consent, have an acute presenting complaint, be aged 18 years or older, and use any of the following: smartwatch, activity tracker, or other wearable monitoring devices, or a smartphone that collects step counts or data from other wearable devices.

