**Exclusion criteria**
Patients who are unable to give informed consent or endure an imminently life-threatening illness.

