**Main study end point**
To quantify the proportion of patients assessed for an acute complaint who are wearing a device that collects data on vital signs (ie, heart rate and step count).

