### Study Procedures

All patients aged 18 years and older who present to acute care will be asked if they wear a smartwatch, activity tracker, or wearable that measures heart rate.

Patients will be asked to give informed consent in line with the guidance from the participating countries. This is likely to include written informed consent in the Netherlands, Denmark, and the United Kingdom. Informed consent will be explicit about accessing data from patient-held wearables (Multimedia Appendix 1). Once consent has been obtained, initial data will be entered into the case report form, and the remaining items of the case report form will be completed on the day after the initial presentation or later (Textbox 3). Study documentation will include a guide for investigators to interrogate commonly used wearable devices (Multimedia Appendix 2). Parameters recorded will vary according to the different devices used but should at least include heart rate and step count.

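### The main proportion has two denominators: all adults presenting with an acute complaint in some sections, only eligible patients in others

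*Protocol article*

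**What the plan says.** Several parts of the protocol article use a broad population. The main study end point (Textbox 2) is "To quantify the proportion of patients assessed for an acute complaint who are wearing a device that collects data on vital signs". Study Procedures says "All patients aged 18 years and older who present to acute care will be asked if they wear a smartwatch, activity tracker, or wearable". Governance asks units to collect data on everyone presenting in the study areas over 24 hours.

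Two other parts use a narrower one. Recruitment and Consent says "Patients eligible for inclusion are asked if they use a smartwatch or other wearables that measure heart rate by a collaborator of the study", and adds that a yes completes the inclusion criteria. Primary Outcome Measures defines the primary outcome as "feasibility as assessed by the proportion of eligible patients with emergency presentations who have devices as well as recruitment and retention rates".

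Eligibility is set in Textbox 2. Besides adult age, an acute complaint and ability to consent, a participant must "use any of the following: smartwatch, activity tracker, or other wearable monitoring devices, or a smartphone that collects step counts", or one that collects data from other wearables. The exclusions are "Patients who are unable to give informed consent or endure an imminently life-threatening illness".

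**The concern.** The main result is a single proportion, so its meaning depends on the denominator. Here the article gives two rules that cannot both hold. This goes beyond detail left to a fuller document, because both rules are stated and they disagree.

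The difference affects interpretation. The primary objective is feasibility in acute care, and a reading that depends on the patient's consent and help is hardest to obtain from someone who lacks capacity or is in extremis. If such patients are never asked, the result answers a narrower question than the main end point poses. Sites in four countries that followed different sections would also contribute proportions over different populations to one pooled figure. The article's Conclusions intend the results to support power calculations for later studies, which would carry the ambiguity forward.

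**Working it through.** **Sections side by side**

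| Section | Who is asked or counted |
|---|---|
| Main study end point (Textbox 2) | everyone assessed for an acute complaint |
| Study Procedures | all presenting adults |
| Governance | everyone presenting in the study areas in 24 hours |
| Recruitment and Consent | eligible patients only |
| Primary Outcome Measures | eligible patients only |

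**Two readings of eligible**

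1. *Literal.* Every eligible patient uses a device, because Textbox 2 requires it. If the numerator counts the same devices as the inclusion criterion, numerator and denominator coincide and the proportion is 100% by construction.
2. *Eligible apart from device use.* The remaining conditions are age, an acute complaint, ability to consent and no immediate threat to life. Patients who fail either of the last two leave the denominator, although the main end point and Study Procedures include them.

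**The plan's own figure.** Sample Size Calculation gives 40 hospitals × 50 patients = 2000 screened, which reproduces. It is a count of patients screened, not a precision calculation, and does not say which denominator applies.

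**Illustration only.** Inputs from Results: 1137 screened and 452 included, in 34 hospitals.

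- Included over screened: p = 452/1137 = 39.8%. The 1137 − 452 = 685 not included are not split by reason, so this ratio only stands in for device use among those asked.
- Standard error under simple random sampling: √(0.3975 × 0.6025 / 1137) = 1.45 points; 95% half-width 1.96 × 1.45 = 2.8 points. This ignores clustering by hospital.

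Let f be the share of presenters not asked and q their device use. Neither is given in the documents. The all-presenter proportion is (1 − f)p + fq, and the bias from reporting p instead is f(p − q).

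| f (assumed) | q = 0 (lower bound) | q = 20% | q = 39.8% | q = 50% | q = 100% (upper bound) |
|---|---|---|---|---|---|
| 5% | 37.8% | 38.8% | 39.8% | 40.3% | 42.8% |
| 10% | 35.8% | 37.8% | 39.8% | 40.8% | 45.8% |
| 20% | 31.8% | 35.8% | 39.8% | 41.8% | 51.8% |
| 30% | 27.8% | 33.8% | 39.8% | 42.8% | 57.8% |

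For example, with f = 10% the lower bound is 0.90 × 0.3975 + 0.10 × 0 = 35.8% and the upper bound is 0.90 × 0.3975 + 0.10 × 1 = 45.8%. Reporting p overstates the all-presenter figure when q is below p, is unbiased when q equals p, and understates it when q is above p.

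**The case against.** The strongest defence is that Recruitment and Consent is loosely worded. Its next sentence treats a yes as completing eligibility, so the term cannot be meant literally and may just mean the target population. That paragraph mentions neither capacity nor severity, and the two operational sections, Study Procedures and Governance, agree with each other. This has some force: a prior filter on capacity and severity is the most natural non-literal reading, but the text does not force it. It does not remove the conflict, because Primary Outcome Measures also counts over eligible patients. Under that definition, leaving out patients who cannot consent is the stated denominator and not an error.

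A reader might go further and infer that the main proportion is inflated by several points or several standard errors. The documents do not support that. The share not asked and their device use are both assumed. The Conclusions voice concern only about ownership by age and wealth, not by capacity or acuity. The 452 are inclusions, which also require consent, not device users. If screening followed Study Procedures, the 1137 may already contain patients who could not be asked, and scaling by (1 − f) would subtract them twice. A multiple of the simple-random-sampling standard error would also ignore clustering in 34 hospitals.

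How to code a patient who cannot answer is detail that a condensed article may leave to the full protocol or case report form. Its absence is not part of this point.

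**Conclusion.** The point holds as an inconsistency in the current text. The denominator of the main proportion is stated as all presenting or assessed adults in three places and as eligible patients in two. Of the two readings of eligible, one makes the proportion trivial and the other limits it to patients who could be asked. Neither is the quantity named in the main study end point.

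No bias is established in either direction or size. Overstatement follows only if patients not asked use devices less than those asked. The table shows what would be at stake under assumed values: at 10% not asked, the bounds span 10 points (35.8% to 45.8%), against a sampling half-width of 2.8 points before allowing for clustering. This is worth correcting because the proportion is the headline result and the correction is cheap.

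**What to change.** 1. Reconcile the main study end point, Study Procedures, Primary Outcome Measures, Recruitment and Consent, and Governance to one denominator: all adults presenting with an acute medical complaint in the collection period, not conditional on device use.
2. State which rule sites followed and who the 1137 screened patients are.
3. Report the proportion with an explicit label saying that it is among patients asked.
4. Where counts of patients not asked were logged, add bounds for all presenters, counting those patients first as non-users and then as users.
5. Keep availability of usable device data as a separate feasibility measure. Scoring patients who could not be asked as having no usable data would change the main end point's numerator: someone who lacks capacity but is wearing a device counts as a wearer.

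The cost is a wording change and one extra reported line, with a possibly less favourable headline figure. The abstract and Results show that data collection has finished, so a tally of patients not asked can be introduced only for future or repeated collection; where no counts were logged, only the labelling and the statement of the rule remain possible.

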#### Governance

Hospitals will be recruited across Europe and coordinated by the study steering board. The study steering board consists of the principal investigators and members of the Safer home consortium. Centers are encouraged to collect data on a small cohort of patients before the main study week (May 10-22, 2024). During the main study week, all participating units are asked to collect data on all patients presenting in the study areas during a 24-hour period.

Participating countries will be responsible for their own submission for approval and coordination of research.

## Results

Approvals have been completed in 11 sites in Denmark, 17 sites in the Netherlands, 1 site in Switzerland, and 7 sites in the United Kingdom.

The main FUSE study has gone live on the May 15, 2024, in 34 hospitals in the Netherlands (n=17), the United Kingdom (n=7), Denmark (n=9), and Switzerland (n=1). A total of 1137 patients were screened, of these, 452 patients were included and 209 patients had data on at least 2 collection points, allowing for an analysis of trends.

Preliminary analysis will be completed by December 31, 2024, and the main manuscript will be submitted for publication by the end of March 2025.

## Discussion

### Anticipated Findings

While sensors that can be carried or worn are in widespread use with a project market size in 2023 of in excess of US $4 billion [20], previous research has found little evidence of their use in emergency care [21]. This study aims to determine if there are opportunities to use the data generated by these consumer-held devices to improve patient care. Trends in vital signs and mobility are used to quantify risks to patients and are likely to become more important as the proportion of patients with chronic conditions (and abnormal vital signs during signs of clinical stability) is increasing. For clinical use we anticipate a number of use cases: Assessing patients whose vital signs have not changed in the week previous presentation in an acute care setting might reassure clinicians that the condition is overall stable and that treatment in the community is likely to be safe. Assessing patients whose vital signs have significantly changed in the days or hours before presentation might increase the confidence of clinicians to admit for observation and treatment in the hospital. This type of decision-making is commonly undertaken during an initial observation phase in emergency departments or acute medical unit with patients being observed for a night before committing to a decision about admission or discharge. We anticipate that this type of decision-making could be undertaken during the initial presentation if data on markers of physiological instability is available already at this point.

### Limitations

The distribution of wearables in the population might point toward the exclusion of a significant proportion of the population from this type of support: patients who are less financially well off or not sufficiently digitally or health literate might be disadvantaged in a future health care. This data will hence be collected as part of FUSE. While this study focuses on readily available data and will require in future supplementation by detailed qualitative data.

The study is conducted by a group of secondary care clinicians with expertise in medical emergencies. Many of the patients who will be screened and included will have previously presented in primary care. There is no theoretical reason that the results from this study might not be applicable to those presenting in primary care, but this might require future research.

In preparation of the study, we reviewed sales for the top 20 devices in the Dutch and British markets. For these devices, we have created a data dictionary for investigators that will enable them to assist patients in the location of relevant data. With new devices coming online and changes in consumer habits, the frequency distribution of these devices might however be soon outdated.

The study will explicitly not address the quality of data collected in wearables. We will, however, report on the distribution of devices and approval for medical use where applicable. In the same vein, we anticipate that the duration of usage by individuals will affect the measurements. This is something that we might not be able to evaluate in the current setup.

Given that patients will use a range of devices with different methods for data acquisition and different usage patterns our analysis will focus on the comparison of relative changes in parameters for individuals (intraindividual variation). This relies on the assumption that individuals will have a pattern of usage that is constant over time. Further research will be required, especially if it turns out that the variation between the collected parameters turns out to be large in the days before deterioration and presentation to the hospital.

Finally, future health care needs to be equitable. FUSE will include data that will allow us to gauge some aspects of equity, diversity, and inclusion which are crucial for the development of policy and strategy in this field.

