**Secondary objectives**
To explore the proportion of patients assessed for an acute complaint who are wearing or carrying a device that collects data on vital signs (eg, smartwatch or other wearables).To describe the population who wear or carry devices that collect data on vital signs.To quantify the change in heart rate in patients admitted to acute care between measurements taken on presentation and previously recorded vital signs by a consumer-grade wearable while patients were stable and well.To quantify the change in step count in patients admitted to acute care between measurements taken shortly before presentation and previously recorded step counts by a consumer-grade wearable while patients were stable and well.To explore the association between trends in in vital signs with the disposition of patients (admission to a general ward, critical care area, or discharge home within 24 hours from assessment).

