**Secondary study end points**
Secondary end points will focus on four areas of interest:The difference between the heart rate at rest from the wearable device 24 hours, 1 week, and 1 month before assessment by emergency practitioners compared with the first set of vital sign parameters measured on admission to acute care.The change in daily steps taken in the month before admission to acute care.To describe the population that is wearing devices that collect data on vital signs in terms of gender, age group, severity of illness as measured by a standard set of vital signs, level of education, and digital literacy and frailty.To explore the association of changes in heart rate from the community to assessment in acute care services with clinical end points such as admission to a general ward or admission to a critical care area or discharge home within 24 hours from the time of clinical assessment.

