Data items were collected as part of the "Feasibility of Using resting heart rate and step counts from patient-held Sensors during clinical assessment of medical Emergencies" (FUSE) study.Site ID is the unique number for each site.Participant ID is a consecutive number (no identifiable information is collected).Location is the location where the patient is included in the study (ie, emergency department, medical admissions unit, ambulatory emergency care, or other).Sex as reported by the patient (ie, men, women nonbinary, or unknown).Date of birth, which will be used to compute an age category.Date and time of first presentation, defined as the time that a patient presents at the location.Highest level of education is the patient finished highest level of education or the level of education the patient is currently following (ie, primary school, secondary school, and higher education).Digital literacy is assessed using 2 questions asking for confidence of using the internet and confidence of using mobile apps, which patients can answer using a 5-point Likert scale.Device is the device used to measure heart rate, and the brand and type will be recorded.Phone is the phone that patients use, and this will be used to retrieve the step count and heart rate data. The brand and type will be recorded.Heart rate on the device is the heart rate that is stored and measured by the device, and the resting heart rate (as presented by the device), the minimum, maximum, and mean or median (depending on the device) will be retrieved on three-time points, namely on presentation, within 24 hours before presentation and within 1 week (plus or minus 1 day) before presentation.Walking distance is the number of steps of exact distance (in kilometers or miles), either measured by the device of the phone. The daily walking distance of the 7 days before the presentation will be recorded.Frailty as quantified through the Clinical Frailty Scale [19].Mobility will be assessed as either normal or impaired. Mobility is considered impaired if the patient is unable to get onto the bed unaided, either from the ambulance gurney or whichever way they arrive.Date and time of the first set of vital signs is defined as the time that the first set of vital signs are measured.Heart rate on admission is the first heart rate measured during clinical examination.National Early Warning Score [9] as a standardized assessment of the severity of illness, based on the first full measurements of respiratory rate (per minute), oxygen saturation (in %), temperature (in °C), heart rate (per minute), systolic blood pressure (in mm Hg), AVPU (alert, verbal, pain, and unresponsive) score, and the use of any supplemental oxygen.Outcome is assessed at midday on the day after the initial assessment and can be (ie, discharged, admitted to hospital, admitted to high care or intensive care, or deceased).

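### The step-change end point depends on device use staying constant up to presentation, and no listed data item shows whether the device was worn or carried.

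*Protocol article*

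**What the plan says.** One secondary objective is this: "To quantify the change in step count in patients admitted to acute care", comparing "measurements taken shortly before presentation and previously recorded step counts by a consumer-grade wearable while patients were stable and well". The matching item under Secondary study end points reads: "The change in daily steps taken in the month before admission to acute care".

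The data items listed under Study Procedures describe the step data: "The daily walking distance of the 7 days before the presentation will be recorded". The figure may come from the wearable or from the phone. The list has no item on whether either was worn or carried on a given day. It does include device heart rate on presentation, within 24 hours before it, and at 1 week (plus or minus 1 day) before it.

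Data Analysis compares averages or medians across time points and tests an interaction of time, disposition and change in steps. It also says that missing values are not imputed.

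Limitations states that the analysis concentrates on relative change within individuals and adds: "This relies on the assumption that individuals will have a pattern of usage that is constant over time". Just before that it says: "we anticipate that the duration of usage by individuals will affect the measurements", followed by: "This is something that we might not be able to evaluate in the current setup".

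**The concern.** A within-person comparison removes differences in device use that are stable between people. It does not remove a change in use that begins with the illness, and the days just before presentation are the days this end point studies. That people use a watch or phone less when unwell is an inference, not a statement in the article, but it is plausible. If it happens, the assumption is weakest where the end point is measured.

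Less use lowers recorded steps, which is the direction of the effect sought. If it is commoner in patients who are then admitted, it also feeds the test by disposition. Limitations calls for further research if variation before presentation proves large, but a real fall in walking would look the same, so that trigger cannot separate the two. The Conclusions section says the results should aid power calculations for later studies, so an inflated step change would carry forward.

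**Working it through.** The article gives no planning figure for step change and no figure for non-use, so there is nothing to reproduce. Every rate of non-use below is an assumption.

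**1. Partial use.** Let t be the true proportional change in steps and w the share of usual wear or carry time near presentation, with usual use at baseline. Apparent change = (1 + t) × w − 1.

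| True change t | w = 0.75 | w = 0.50 | w = 0.25 | w = 0 |
|---|---|---|---|---|
| 0 | −25% | −50% | −75% | −100% |
| −20% | −40% | −60% | −80% | −100% |

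**2. Complete non-use entered as zero.** Suppose walking is unchanged, a fraction q of patients do not use the device near presentation, nobody is a non-user at baseline, and non-use is unrelated to usual step level. Mean change = (1 − q) × 0 + q × (−100%) = −100q%. For q = 0.05, 0.10, 0.20 and 0.30 this gives −5, −10, −20 and −30 percentage points.

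**3. Non-use at baseline as well.** With fractions q0 at baseline and q1 near presentation, change in mean steps = (1 − q1)/(1 − q0) − 1. For q0 = 0.10 and q1 = 0.30 this is 0.70/0.90 − 1 = −22%, not −30%. For q0 = q1 it is 0. What matters is the change in non-use.

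**4. Mean or median.** In step 2 with q = 0.30, 70% of patients have a change of 0 and 30% have −100%. The mean is −30% and the median is 0. Data Analysis allows either summary.

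**5. Difference by disposition**, under the conditions of step 2:

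| Admitted q | Discharged q | False difference |
|---|---|---|
| 0.10 | 0.05 | −5 points |
| 0.20 | 0.10 | −10 points |
| 0.30 | 0.10 | −20 points |
| 0.20 | 0.20 | 0 |

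**6. Days left blank.** The value is then missing and not imputed. Steps 2 to 5 do not apply. The problem becomes one of selection: patients whose use stopped with the illness leave the step analysis.

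**7. What the collected data can check.** A heart-rate value from a wearable in a window shows that it was worn at some point in that window. Two pre-presentation windows have such a value, so the 24-hour versus 1-week step comparison can be partly checked. The other step days cannot, and neither can steps counted by a phone.

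**The case against.** The strongest reply is that the authors disclose the assumption, say that the study does not address the quality of wearable data, and present a feasibility study whose primary outcome (device ownership, recruitment, retention) is untouched. Rules for valid days commonly sit in an analysis plan or full protocol, and the investigators' device guide in Multimedia Appendix 2 is not shown. All of this stands, and it keeps the point to a secondary end point. It does not remove the point. Disclosure does not correct a bias, and an analysis plan cannot recover use on days for which the form, as listed, asks nothing. The partial check in step 7 also shows that the setup can evaluate more than Limitations suggests.

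A reader might infer something stronger: that non-use is recorded as lost mobility, by some definite amount. The documents do not support that. Nothing shown says whether a day without use is entered as zero or left blank. Results reports trend data for 209 of 452 included patients (46.2%), so data were absent for many, but it gives no reason. The end points are worded as step count, and bedside mobility is a separate item that non-use does not affect. No rate of non-use is given, overall or by disposition.

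**Conclusion.** The concern holds in a limited form. The step-change end point and its test by disposition rest on constant device use, and the listed data items cannot tell less use from less walking. Depending on how a non-use day is entered, the result is an apparent fall in steps or selective missingness.

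The size is unknown. The 5 to 30 point shifts are illustrations that require zeros to be entered, no non-use at baseline, non-use unrelated to usual step level, and analysis by means. A false difference by disposition requires the change in use to differ between the groups. The concern justifies a sensitivity analysis and careful wording of the step results. It does not bear on the primary feasibility outcome.

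**What to change.** - **Wearable steps.** Add a sensitivity analysis that repeats the 24-hour versus 1-week step comparison, overall and by disposition, only in patients whose same wearable has a heart-rate record in both windows. Treat steps in a window without a record as missing. Report the share excluded by disposition.
- **State its limits.** A heart-rate record shows some wear, not full-day wear, and the check does not extend to phone-counted steps.
- **Phone steps.** Describe results as change in recorded steps, and show them with and without zero-step days.
- **Later data collection.** Add one case report form question: on which of the last 7 days was the device not worn or carried as usual? This cannot serve patients already enrolled, because the abstract and Results place data collection in May 2024.

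The first three need no new data. The cost is fewer patients in the sensitivity analysis, from the 209 with data at two or more collection points. Dropping zero-step days also removes days on which a patient truly did not walk, so both phone results should be shown together.
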